# Early non-invasive ventilation for acute respiratory failure in immunocompromised patients (IVNIctus): study protocol for a multicenter randomized controlled trial

**DOI:** 10.1186/1745-6215-15-372

**Published:** 2014-09-25

**Keywords:** Non-invasive ventilation, Immunocompromised patient, Acute respiratory failure

## Abstract

**Background:**

Acute respiratory failure (ARF) remains the leading reason for intensive care unit (ICU) admission of immunocompromised patients. In the most severe cases, high-flow oxygen therapy may fail to ensure adequate gas exchange, and mechanical ventilation (MV) must be used. This scenario is associated with high mortality rates of 40 to 60%, depending on the cause of ARF and type of immune deficiency. The use of non-invasive ventilation (NIV) in this situation has been criticized as potentially delaying the initiation of optimal treatment. In contrast, early NIV used prophylactically in patients with ARF who do not meet the criteria for invasive MV (IMV) may obviate the need for IMV, thereby decreasing the morbidity and mortality rates. We aim to demonstrate that a management strategy including early NIV decreases 28-day mortality rates compared to oxygen therapy alone in immunocompromised patients with ARF.

**Methods/Design:**

This is a multicenter parallel-group randomized controlled trial comparing early NIV to oxygen therapy alone in immunocompromised patients with ARF. All immunocompromised adult patients admitted to admission for ARF are eligible for randomization. Patient with ARF onset more than 72 hours earlier or ARF related to cardiogenic pulmonary edema or hypercapnia, or with a need for immediate endotracheal intubation or other organ failure are not eligible.

After inclusion patient are allocated to receive early NIV (intervention arm) or oxygen therapy only (control arm).

We plan to enroll 374 patients in 29 ICUs. An interim analysis is planned after the inclusion of 187 patients. The main objective is to demonstrate early NIV increases survival as compared to oxygen therapy alone. Other outcomes include the need of IMV, organ failure evolution, nosocomial infections rate, 6 months survival.

**Discussion:**

This study is expected to demonstrate an improved 28-day survival in immunocompromised patients managed with early NIV.

**Trial registration:**

Registration number: Clinicaltrials.gov NCT01915719. Registered on 26 July 2013.

**Electronic supplementary material:**

The online version of this article (doi:10.1186/1745-6215-15-372) contains supplementary material, which is available to authorized users.

## Background

Acute respiratory failure (ARF) in immunocompromised patients is both common and severe
[1]. ARF is the leading cause of ICU admission in patients with hematological or solid malignancies. The most recent studies have found mortality rates of nearly 50% in this population
[1–3]. Mortality rates are highest in patients with severe respiratory distress requiring invasive mechanical ventilation (IMV). In this situation, mortality can reach 40% in organ transplant recipients and patients receiving immunosuppressive treatments
[4], and 60% in patients with hematological or solid malignancies
[1–3].

Noninvasive ventilation (NIV) via a mask was introduced in the 1990s with the primary goal of decreasing the need for IMV and the rate of IMV-related complications. NIV has been chiefly evaluated in two indications: (a) as an alternative to IMV in patients with severe ARF meeting criteria for IMV, and (b) as a means of avoiding IMV in patients with ARF who do not meet criteria for IMV. The use of NIV in patients with severe ARF has been criticized, as the failure rate is nearly 50% among immunocompromised patients and excess mortality occurs among patients who receive delayed IMV
[5–7]. Some studies even found improved survival after early IMV
[5, 6, 8]. NIV is an accepted treatment when criteria for IMV are not met, although the underlying level of evidence is low
[9–12]. A single randomized trial in 52 patients established that early NIV improved survival in immunocompromised patients
[11]. However, this study has three major flaws: (a) the patients were recruited at a single center; (b) the mortality rate among patients managed with IMV was 90%, which is considerably higher than current rates; and (c) acute illness severity varied across patients, with some patients apparently meeting criteria for IMV at baseline and others having no criteria for severe ARF. Nevertheless, the beneficial effect of NIV on survival was impressive: mortality was 81% without NIV and 50% with NIV. The result of an Italian study of 40 solid organ transplant recipients supports the beneficial effect of postoperative NIV on survival
[12].Figure 
1 illustrates these data by showing the results of studies reporting outcomes of immunocompromised patients with ARF. We compared hospital mortality in patients managed with oxygen alone and in patients given NIV.

**Figure 1 Fig1:**
[figure not shown]
**Outcomes associated with the in-ICU use of non-invasive ventilation in immunocompromised patients.** Adapted from Azoulay E, ^13^.

This forest plot figure represents cohort studies or trials reporting both patients receiving oxygen or NIV. Studies are presented with first author name, year of publication (number of patients treated with oxygen only and number of patients receiving NIV and oxygen). Odd Ratio (OR and [95% CI] comparing mortality associated with the use of NIV.

These studies include: two randomized ICU trials comparing two strategies for managing immunocompromised patients with ARF (Antonelli and Hilbert)
[11, 12]; a 2004 prospective nonrandomized trial evaluating the impact of ARF in patients with hematological or solid malignancies (Azoulay)
[1]; an ICU study in non-intubated patients with ARF randomized to two different diagnostic strategies (Azoulay)
[13]; a retrospective study of ICU patients with ARF managed with oxygen only or NIV (Depuydt)
[14]; and a 2011 multicenter Italian observational ICU study of patients with hematological malignancies and ARF (Gristina)
[15].

This literature review shows no difference in mortality rates between patients managed with oxygen only and those given NIV. However, none of these studies provides a sufficient level of evidence. In addition, patients in whom ARF was combined with other organ failures were not separated from those with isolated ARF. This is an important point, as the risk of mortality is known to increase with the number of organ failures and the severity of the ARF. Overall, these studies suggest that NIV may be useful as a prophylactic treatment to obviate the need for IMV. In contrast, the use of NIV as an alternative to IMV in patients with severe ARF seems to adversely impact survival.

We have planned a multicenter randomized controlled trial in immunocompromised patients with ARF. This trial will be carried out in 29 specialized ICUs in France and Belgium (in teaching hospitals, community hospitals, and national cancer network hospitals) with high admission rates of immunocompromised patients. The study objective is to demonstrate that incorporating early NIV into the management strategy for patients with ARF who do not meet criteria for IMV improves survival compared to oxygen only.

## Methods/Design

The IVNIctus trial is a prospective, multicenter, open-label, randomized controlled trial comparing a management strategy including early NIV with oxygen alone in immunocompromised patients admitted to ICU with ARF. Early NIV is defined as NIV treatment for patients with ARF who are without any other organ failure or intubation criteria (intubation criteria would be described further (in patient management bias paragrah)).

The study hypothesis is that early NIV decreases mortality in immunocompromised patients requiring ICU admission for ARF. The primary evaluation criterion is survival on day 28 after randomization. Secondary evaluation criteria are proportion of patients treated with IMV in each group, number of organ failures (Sequential Organ Failure Assessment score) 72 hours after randomization in each group, invasive mechanical ventilation duration and ICU stay length in each group, patient comfort in each group, frequency of nosocomial infections in each group, survival at six months after randomization.

The primary study objective is to demonstrate that in immunocompromised patients admitted to the ICU with ARF, a management strategy including early NIV improves 28-day mortality compared to high-flow oxygen without NIV.

### Ethics

The study was approved by the local independent ethic committee (Comite de protection des personnes CPP Ile de France IV, Saint Louis on 21 May 2012, number 2012/11SC), the French health authorities (AFSSAPS) on 11 5 2011, number EudraCT 2011-A00591-40. The University Hospital of Paris (AP-HP) is the sponsor of the trial. Informed consent will be obtained from each participant.

### Eligibility criteria

Only patients meeting all inclusion criteria may be included. Inclusion criteria are as follows: age >18 years; ICU admission; immune deficiency due to any cause (solid organ transplantation, hematological or solid malignancy under treatment or in remission for less than five years, or immunosuppressive treatment defined as corticosteroid therapy (1 mg/Kg/day prednisone equivalent or corticosteroid therapy for longer than one month) or use of another immunosuppressant drug (in a high dosage or for longer than one month); ARF (other than during the postoperative period after cancer surgery) defined as hypoxemia <60 mmHg on room air and/or clinical evidence of respiratory distress (intercostal recession or polypnea >30/min or dyspnea at rest); and onset of ARF within the last 72 hours.

Patients meeting any of the following exclusion criteria will be excluded from the study: hypercapnia >50 mmHg or greater than 10 mmHg PaCO_2_ increase after oxygen therapy initiation, requirement for immediate IMV, probable cardiogenic acute pulmonary edema, requirement for vasoactive therapy (epinephrine or norepinephrine >0.3 μg/Kg/min), impaired consciousness (Glasgow Coma Scale score <13), do-not-intubate decision, long-term oxygen therapy, refusal of the patient or family to provide consent to the study, ongoing myocardial infarction or acute coronary syndrome, pregnancy or breastfeeding or absence of coverage by the French statutory health insurance system.

### Description of the study methodology

#### Study arms

The control group will consist of patients included in the study and allocated at random to the arm managed with oxygen but no NIV. In patients requiring intubation, use of NIV to secure the procedure is allowed. The intervention group will consist of patients included in the study and allocated at random to the arm managed with one hour NIV sessions in addition to oxygen. A total of six hours is required on the first day.

### Patient recruitment modalities

All 29 recruiting ICUs (Additional file
1: Table S1) have considerable experience and expertise in the management of immunocompromised patients. The 29 ICUs participating in the study each admit 50 to 200 immunocompromised patients per year, including the 10 to 20% who meet IVNIctus trial eligibility criteria. Consecutive patients admitted to these ICUs and meeting all the inclusion criteria and none of the exclusion criteria will be included into the trial.

### Randomization and study treatment

Eligible patients will be randomly assigned, in a 1:1 ratio, to one of the two treatment arms. Randomization will occur either at ICU admission or when the eligibility criteria are met if the patient was admitted for a reason other than ARF. Randomization will be performed via the website telemedicine cleanweb.aphp. After having completed the randomization webpage, the investigator will receive the treatment arm designation. Time zero will be defined by randomization time. Randomization will be stratified by center, oxygen flow rate at randomization (>or ≤9 L/min), and reason of immunosuppression (oncologic and hematologic malignancy or immunosuppressed treatment and solid organ transplantation). All the data will be notified in an e-CRF on the website telemedecine cleanweb.aphp.

In the early NIV group (intervention group), NIV sessions will be administered throughout the 24-hour cycle, with oxygen therapy sessions in the intervals, the objective being to maintain SpO_2_ > 92%. NIV would be given for at least six out of 24 hours during the first 24 hours. In the oxygen-only group (control group), continuous oxygen therapy will be provided to maintain SpO_2_ > 92%.

### Treatments and procedures allowed during the trial

#### Bronchoalveolar lavage

BAL may be performed under NIV in both groups if required by the patient’s condition. The efficacy and safety of an NIV session used to perform bronchoscopy have been evaluated previously
[16]. NIV duration and parameters will be recorded in the patient’s case report form.

#### Preoxygenation before intubation

This technique consisting in a NIV session immediately before endotracheal intubation has been shown to decrease the decline in oxygen saturation during intubation
[17]. It may be used in both groups.

#### Intravenous treatments

Participation in the trial does not result in any restrictions in the use of specific treatments required by the patient’s underlying disease and/or ARF.

### Detailed description of the conduct of the study

Figure 
2 shows a diagram of the study procedures.

**Figure 2 Fig2:**
[figure not shown]
**Study diagram.** ARF, acute respiratory failure; NIV non-invasive ventilation.

Table 
1 summarizes the clinical and laboratory test performed throughout the study.

**Table 1 Tab1:** **Clinical and laboratory data**

	Clinical data	Laboratory data
To: randomization	Underlying disease	
	ARF characteristics	
First 24 hours	Respiratory rate, SpO_2_, oxygen flow or FiO_2_	
Day1 to Day7, Day14, Day28	Respiratory data	SOFA score
	Course of respiratory and other organ failure	
	Suspected diagnosis every day	
	Tolerance of NIV in NIV group	
	Intubation criteria in both groups	
Day28	Mortality	
	Diagnosis of ARF	
	Respiratory investigations	
	Hospital acquired infections	
Day180	Mortality	

SpO2: oxygen pulse saturation; FiO2: inspired oxygen fraction; SOFA: Sequential Organ Failure Assessment; ARF: acute respiratory failure; NIV non-invasive ventilation, T0: time of randomization.

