### Evaluation at study inclusion (T0)

The evaluation at study inclusion will consist of clinical characteristics of the patient, underlying disease, disease responsible for ARF, and investigations usually performed at ICU admission of immunocompromised patients with ARF.

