### Evaluations during study participation

Evaluations performed during study participation will consist of respiratory characteristics (respiratory rate, SpO2, oxygen flow or FiO2) every hour within the first 24 hours; data to assess the disease course on day 1, 2, 3, 4, 5, 6, 7, 14, and 28 (the worst value will be recorded); clinical data; results of investigations; and data on NIV tolerance and efficacy.

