### Statistical analysis

The analysis will be performed according to the intention-to-treat approach. We will use the chi-square test to compare 28-day mortality rates in the group managed with oxygen only and in the group managed with oxygen and early NIV. Randomization will be stratified on the underlying disease (hematological or solid malignancy versus other) and on ARF severity as assessed by the baseline oxygen flow rate (≤9 L /min versus >9 L/min to obtain SpO_2_ > 95% and/or resolution of the signs of respiratory distress). We will test for an interaction between the treatment effect and the underlying disease. If such an interaction is found, we will use the chi-square test to look for a treatment effect within the stratification subgroups. We will correct for the multiple comparisons using the Bonferroni test (error of first order 0.025). Similarly, we will look for an interaction between the treatment effect and baseline ARF severity. If such an interaction is found, we will use the chi-square test to look for a treatment effect within the stratification subgroups. We will correct for the multiple comparisons using the Bonferroni test (error of first order 0.025).

For the secondary evaluation criteria, we will use the chi-square test to compare the proportions of patients with treatment failure (defined by the need of IMV), and nosocomial infection in the two treatment arms. The procedure described above for potential subgroup analyses of the primary evaluation criterion will be used for these secondary evaluation criteria. Wilcoxon’s test will be performed to compare the number of organ failures (SOFA score) between the two arms 72 hours after study inclusion. Median hospital and ICU length of stay will be compared between the two arms using the Kaplan-Meier estimator, with discharge alive as the event of interest and death as the censoring event. Time on invasive mechanical ventilation will be compared between the two arms using the log-rank test.

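### SOFA is first scheduled as a day-1 worst value and none is named at T0: the 72-hour comparison stays valid but loses precision, and organ-failure evolution lacks a clean scheduled baseline

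*Protocol article*

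**What the plan says.** **Schedule.** Table 1 has a separate row for randomisation, labelled "To: randomization". It lists underlying disease and ARF characteristics, and its laboratory cell is empty. SOFA appears once in the table, in the row "Day1 to Day7, Day14, Day28". The section Evaluations during study participation covers the same days and adds that "the worst value will be recorded".

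**Inclusion.** The section Evaluation at study inclusion (T0) does not name SOFA. It does cover clinical characteristics and the "investigations usually performed at ICU admission of immunocompromised patients with ARF".

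**Timing.** Under Randomization and study treatment, "Time zero will be defined by randomization time". The same section requires at least six hours of NIV in the first 24 hours in the intervention arm. Day 1 is not defined.

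**Endpoint and analysis.** The abstract lists "organ failure evolution" among the outcomes. The opening of Methods/Design in the main text defines the secondary criterion as the SOFA level 72 hours after randomisation. The Statistical analysis section uses Wilcoxon's test to "compare the number of organ failures (SOFA score) between the two arms 72 hours after study inclusion", with no covariate.

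**The concern.** A change in organ failure needs a starting value that allocation cannot have influenced. The first scheduled SOFA is a day-1 worst value, and day 1 can include hours of allocated treatment and their consequences, such as early intubation. If that value became the baseline, either in a change score or as a covariate, part of any early treatment effect would be mixed into it.

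The comparison of 72-hour levels does not have this problem, but it uses no information about how ill each patient was at entry. The article's own background faults earlier studies for not separating isolated ARF from ARF with other organ failures, and its discussion repeats the point for organ dysfunction at the start of NIV. A T0 organ-failure score would answer that criticism directly. At stake are the precision of one named secondary endpoint and the interpretation of anything reported as evolution. The primary endpoint is not affected.

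**Working it through.** **Inputs.** The SOFA days and the contents of the randomisation row come from Table 1. The worst-value rule comes from Evaluations during study participation. Time zero and the six-hour NIV minimum come from Randomization and study treatment. The 72-hour level comes from Methods/Design, and the test from Statistical analysis. The documents give no SOFA standard deviation and no correlation between baseline and 72-hour SOFA; both are assumed below.

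**The plan's own figure.** No sample size is stated for SOFA. The only design figure is 187 per arm for 28-day mortality of 35% against 20%, two-sided alpha 0.05 and 90% power. With pooled variance and no continuity correction:

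n = [1.960 × √(2 × 0.275 × 0.725) + 1.282 × √(0.35 × 0.65 + 0.20 × 0.80)]² / 0.15² = 184.1, so 185 per arm.

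Power at 187 per arm is 0.904, so the stated size reproduces. It is used below only as the number per arm.

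**Step 1: is the day-1 value clean?** There are two readings of Day 1.
- The 24 hours after randomisation: the worst value is wholly post-randomisation and covers the period with at least six hours of NIV in one arm.
- A calendar day: the value mixes hours before and after randomisation, in proportions that depend on the time of randomisation.

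Under neither reading is it a pre-treatment score.

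**Step 2: what a day-1 baseline would do.** Let D1 be the effect of allocation on day-1 SOFA and D3 its effect on 72-hour SOFA. A change score from day 1 estimates D3 − D1. Adjustment with slope b estimates D3 − b × D1. Both equal D3 only if D1 = 0, or in the second case also if b = 0. Neither analysis is written in the article.

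**Step 3: is the planned test sound without a baseline?** Randomisation balances baseline SOFA in expectation, so a test of levels does not need it. A simulation of 4,000 null trials with 187 per arm checked this. The SOFA-like scores were assumed: 0.6 × a baseline count with mean 4, plus noise with mean 2 and SD 2.5, rounded and limited to 0 to 24. The unadjusted Wilcoxon test rejected in 4.8% of runs at a nominal 5%.

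**Step 4: what precision is given up?** Linear adjustment for a baseline score with correlation r leaves a fraction 1 − r² of the variance, equivalent to 1/(1 − r²) times the sample. To illustrate power, take a true difference of 0.3 SD (assumed) and 187 per arm:

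power = Φ(0.3 / √[2(1 − r²)/187] − 1.960)

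| Assumed r | Variance reduction r² | Equivalent sample 1/(1 − r²) | Power |
|---|---|---|---|
| none (unadjusted) | 0 | 1.00 | 0.83 |
| 0.4 | 16% | 1/0.84 = 1.19 | 0.89 |
| 0.5 | 25% | 1/0.75 = 1.33 | 0.92 |
| 0.7 | 49% | 1/0.51 = 1.96 | 0.98 |

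These rows compare adjustment for T0 SOFA with no adjustment at all. The formulas are for linear adjustment; for a rank or ordinal model they are only a guide.

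**The case against.** The strongest reply is that nothing stated is invalid. The main text defines the endpoint as a 72-hour level and compares it between randomised arms. No change from day 1 and no day-1 covariate is planned, and evolution is a word of the abstract. This stands: the planned analysis contains no bias to correct on this account.

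A reader might infer that the trial has no pre-randomisation organ-failure data. The documents do not support that. The T0 evaluation includes clinical characteristics and the usual admission investigations, from which a baseline SOFA may be derivable; the article simply does not commit to deriving it.

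A reader might also infer that the 72-hour comparison cannot be adjusted. That is wrong too. Oxygen flow, reason for immunosuppression and centre are fixed at randomisation, and ARF characteristics are recorded there. Adjusting for them would capture some of the gain shown above, so the table gives upper limits. Entry limits on consciousness and vasopressor dose also narrow the spread of baseline SOFA, which tends to lower r.

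Nor does the missing score mean that compliance with entry cannot be shown. The stated thresholds for circulation and consciousness can be checked without a total SOFA.

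Finally, a journal article condenses a fuller protocol. That would answer a plain omission. Here, though, the article sets out the schedule row by row, with a separate randomisation row that has no SOFA, and it fixes the unadjusted test. If the full protocol already scores SOFA at T0, only Table 1, the definition of Day 1 and the analysis need changing.

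**Conclusion.** The point holds as a low-cost improvement to a secondary endpoint. The first scheduled SOFA is a day-1 worst value from an undefined period that can include at least six hours of allocated NIV, and no SOFA is named at T0. It should not serve as the baseline for organ-failure evolution. The planned Wilcoxon test of the 72-hour level is valid without a baseline, and the loss is precision: at most 16% to 49% of the variance for an assumed correlation of 0.4 to 0.7, and less once the stratification factors are in the model. The power figures also assume a 0.3 SD difference and a 72-hour score for all 187 patients per arm.

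The documents do not support the stronger readings, namely that the 72-hour comparison is biased, that it cannot be adjusted, or that no baseline data exist. That day 1 falls entirely after the start of treatment is likewise an inference, because the article does not define Day 1.

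**What to change.** 1. Add SOFA at T0 to Table 1 and the e-CRF, scored from values timed at or before randomisation, using the routine admission investigations already listed for T0.
2. For patients already included (162 of 374 in the Trial status section), obtain it by chart look-back under the same timing rule. The remaining 374 − 162 = 212 can be scored prospectively. Because the trial is open-label, set the timing rule and the handling of missing components in advance, identically for both arms.
3. Define Day 1 relative to T0.
4. Analyse 72-hour SOFA adjusted for the T0 score, for example by rank analysis of covariance or a proportional-odds model, and keep the unadjusted Wilcoxon test as a sensitivity analysis.
5. State that the day-1 worst value will not be used as a baseline, and either describe the outcome in the abstract as the 72-hour level or define evolution from T0.

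The cost is one short e-CRF page and a look-back through routine records. The downside is a little data entry and some missing T0 components. The primary analysis and the sample size do not change.
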